# N-of-1 Trials of Antimicrobial Stewardship Interventions to Optimize Antibiotic Prescribing for Upper Respiratory Tract Infection in Emergency Departments: Protocol for a Quasi-Experimental Study

**DOI:** 10.2196/50417

**Published:** 2024-02-21

**Keywords:** antibiotic resistance, emergency department, upper respiratory tract infection, N-of-1 trials, prescribing feedback, feedback, emergency, upper respiratory tract, respiratory, antibiotic, antimicrobial stewardship, antimicrobials, antibiotics, hospital, experimental study, antibiotic therapy, URTI, evidence-based intervention, evidence-based, patient education, prescribing rates, patient literacy, Singapore, regression analysis, regression

## Abstract

**Background:**

Antimicrobial stewardship programs attempting to optimize antibiotic therapy and clinical outcomes mainly focus on inpatient and outpatient settings. The lack of antimicrobial stewardship program studies in the emergency department (ED) represents a gap in tackling the problem of antimicrobial resistance as EDs treat a substantial number of upper respiratory tract infection cases throughout the year.

**Objective:**

We intend to implement two evidence-based interventions: (1) patient education and (2) providing physician feedback on their prescribing rates. We will incorporate evidence from a literature review and contextualizing the interventions based on findings from a local qualitative study.

**Methods:**

Our study uses a quasi-experimental design to evaluate the effects of interventions over time in the EDs of 4 public hospitals in Singapore. We will include an initial control period of 18 months. In the next 6 months, we will randomize 2 EDs to receive 1 intervention (ie, patient education) and the other 2 EDs to receive the alternative intervention (ie, physician feedback). All EDs will receive the second intervention in the subsequent 6 months on top of the ongoing intervention. Data will be collected for another 6 months to assess the persistence of the intervention effects. The information leaflets will be handed to patients at the EDs before they consult with the physician, while feedback to individual physicians by senior doctors is in the form of electronic text messages. The feedback will contain the physicians’ antibiotic prescribing rate compared with the departments’ overall antibiotic prescribing rate and a bite-size message on good antibiotic prescribing practices.

**Results:**

We will analyze the data using segmented regression with difference-in-difference estimation to account for concurrent cluster comparisons.

**Conclusions:**

Our proposed study assesses the effectiveness of evidence-based, context-specific interventions to optimize antibiotic prescribing in EDs. These interventions are aligned with Singapore’s national effort to tackle antimicrobial resistance and can be scaled up if successful.

**Trial Registration:**

ClinicalTrials.gov NCT05451863; https://clinicaltrials.gov/study/NCT05451836

**International Registered Report Identifier (IRRID):**

DERR1-10.2196/50417

## Introduction

### Background

The discovery of antibiotics is among the most important public health achievements in the 20th century [1]. However, inappropriate antibiotic use has driven a rapid increase in antibiotic resistance, and with the drying up of the pipeline of new antibiotics, a postantibiotic era is imminent [2-4]. Hence, there is a need to reduce antibiotic use by changing physicians’ antibiotic prescribing practices and reducing patient demand through antimicrobial stewardship programs (ASPs).

Despite the presence of ASPs in various settings, their effects are modest, as antibiotic prescribing practices have been difficult to change [5]. Systematic reviews of interventions to improve physicians’ antibiotic prescribing practices have suggested that the traditional isolated forms of physician education (eg, didactic presentations or printed education materials alone) have only produced slight improvements in prescribing practices [6,7]. However, interventions such as educational outreach or training of local opinion leaders [8,9], as well as behavioral “nudges” in the form of public commitment devices [10] and peer comparison [11], were more effective in improving physician prescribing behaviors. In a systematic review evaluating information leaflets on common infections in general practice, 3 out of 4 studies on antibiotic use showed significant reductions in antibiotic prescriptions [12]. Another study using patient education in the form of an information leaflet regarding antibiotics for bronchitis showed a significant reduction (49% vs 63%) in antibiotic use compared with the control group [13].

### Rationale for the Study

There is a need for more studies to assess the effectiveness of ASP in emergency departments (EDs) [14]. Antibiotics are often prescribed for upper respiratory tract infection (URTI) in the ED, although the routine use of antibiotics for URTI is not recommended [15,16]. A mixed methods study involving 8 EDs in 3 cities in the United States found that the fast-paced environment of the ED encouraged unnecessary antibiotic use [17]. In Singapore, URTIs also accounted for a substantial proportion of attendances at EDs and were associated with frequent ED attendance, as EDs were popular choices for primary care [18]. A previous study at an adult general hospital reported that 35% of adult patients presenting to the ED for URTI were prescribed antibiotics [19].

A physician’s likelihood to prescribe antibiotics for a patient is complex and determined by many factors. The determinants of antibiotic prescribing may include the physician’s worry about complications arising in the patient [20], busy clinical practice [17], insufficient physicians’ knowledge [21], underestimation of the effect of inappropriate antibiotic prescribing leading to antimicrobial resistance (AMR) [22], and perception of the patient’s expectations for an antibiotic [19]. Furthermore, decision fatigue can reduce the physician’s ability to resist ordering inappropriate treatments and increase inappropriate antibiotic prescribing [23].

Given the multifactorial nature of inappropriate antibiotic prescribing, a single approach will unlikely work for all physicians [24]. Furthermore, different patient populations may warrant a variety of interventions. Hence, there is a need for interventions tailored to physicians and patients to promote the judicious use of antibiotics. We describe the protocol of a quasi-experimental study on 2 antibiotic stewardship interventions in the ED according to the SPIRIT (Standard Protocol Items: Recommendations for International Trials) checklist [25].

### Hypothesis and Objectives

We hypothesize that (1) patient education via tailored information leaflets (addressing knowledge, perception, and belief gaps of the local patient population on antibiotic use for URTI) distributed while waiting for consultation with the physician can improve patient knowledge and change patients’ expectations for antibiotics. The change in patients’ expectations of antibiotics would reduce unnecessary antibiotic prescribing by physicians in response to patient demand in time-pressured EDs. (2) Surveillance of antibiotic prescribing rates and physician feedback enables physicians to reflect on their prescribing practices. Physician feedback by senior ED physicians, coupled with education on good antibiotic prescribing practices, serves as a reminder for physicians to improve their antibiotic prescribing practices.

Hence, we aim to evaluate the effectiveness of 2 tailored antimicrobial stewardship interventions in optimizing antibiotic prescribing for uncomplicated URTI cases in 4 adult EDs in Singapore. The two interventions are (1) patient information leaflets on appropriate antibiotic use and AMR. The ED triage nurses will provide pamphlets to patients suspected of URTI prior to their consultation with the physician. The pamphlets are available in Singapore’s 4 official languages. (2) Feedback to physicians on their antibiotic prescribing rates. A senior ED doctor will send a personalized SMS text message to each physician who has seen at least 1 patient in the ED in the previous month at 2 monthly intervals. The feedback will contain the physicians’ antibiotic prescribing rate compared with the departments’ antibiotic prescribing rate and a bite-size message on good antibiotic prescribing practices.

## Methods

### Study Design

Our study uses a quasi-experimental design to evaluate the effects of interventions over time. The entire study period is from January 2021 to December 2023. All 4 EDs will be exposed to 2 interventions over 12 months, with the introduction of each intervention in a 6-month interval. The study will include an initial control period of 18 months, with none of the 4 hospitals exposed to any intervention. In the first 6 months, we will randomly assign 2 EDs to receive 1 intervention (ie, patient education), while the other 2 will receive the second intervention (ie, physician feedback). All EDs will subsequently receive the other intervention in the subsequent 6 months on top of the ongoing intervention. Data will be collected for another 6 months to assess the persistence of the intervention effects (Figure 1).

**Figure 1 figure1:**

Quasi-experimental study of 2 tailored antimicrobial stewardship interventions in 4 emergency departments.

### Study Population

The study population includes physicians working in the adult EDs of 4 public hospitals in Singapore.

### Intervention

We will implement 2 interventions tailored to the context of EDs in Singapore. The interventions were selected based on a literature review of the effectiveness of ASP [12,26] and designed with input from ED physicians within our population via a qualitative study. We consulted senior ED physicians from our study sites to adjust the intervention to the local ED context and to facilitate buy-in prior to study implementation.

### Patient Education

Patient information leaflets were designed to educate patients on appropriate antibiotic use and AMR. The design of the leaflets was based on the information from the United States Centers for Disease Control and Prevention patient educational materials [27] and tailored to the local ED context.

Patient leaflets (Multimedia Appendix 1) were made available at the EDs of the participating sites. ED triage nurses identified patients presenting to the ED with URTI symptoms and provided these patients with the leaflet prior to their consultation with the physician. The leaflets were made available in Singapore’s 4 official languages—English, Chinese, Malay, and Tamil.

### Feedback to Individual ED Physicians by Senior Doctors

A senior ED physician in the department will send the feedback messages to the ED physicians in the institution. The feedback message will contain the physicians’ personal antibiotic prescribing rate and the department’s average prescribing rate in the past month and will be administered at 2 monthly intervals. Bite-sized information on tips to reduce antibiotic prescribing for URTI, obtained from evidence-based sources and adjusted based on inputs from senior ED physicians of our study sites, will be sent together with the personalized message. The feedback will be delivered via Tiger Text, a messaging platform used by employees of Singapore’s public health care institutions.

An example of the message is shown in Textbox 1.

Example of a personalized physician feedback message.Dear Dr X, I would like to share with you the following feedback regarding antibiotic prescribing rates for URTI in TTSH ED. Last month, 200 patients that visited TTSH ED were diagnosed with URTI (primary or secondary diagnosis) and discharged from the ED. Among these patients, 100 (50%) were prescribed with antibiotics.You were the primary physician of 10 patients and 5 (50%) of them were prescribed with antibiotics. I hope this feedback would be useful for your practice. Thank you for being our antibiotic guardian!(Note: Common cold or non-specific upper respiratory tract infection (prominent symptoms include fever, cough, rhinorrhoea, nasal congestion, postnasal drip, sore throat, headache, and myalgia) are caused by at least 200 types of viruses. The receipt of antibiotics for common cold does not reduce the duration of symptoms.)

The medication and visit records of patients diagnosed with uncomplicated URTI will be extracted from the ED’s electronic medical records over 36 months (18 months before and 18 months after the intervention). Patient particulars were deidentified prior to data processing in the R software (R Foundation for Statistical Computing). The medications given to these patients will be identified, and their primary physicians will be given feedback on the antibiotic prescribing rates for the patients they have seen.

Uncomplicated URTI includes but is not limited to acute nasopharyngitis and acute URTI of multiple or unspecified sites (International Classification of Diseases, 9th Revision, Clinical Modification [ICD-9-CM] 460 and 465); acute pharyngitis, tonsillitis, laryngitis, and tracheitis (ICD-9-CM 462, and 463, and 464); and acute or unspecified bronchitis and bronchiolitis (ICD-9-CM 466 and 490). The listed ICD-9-CM codes are for acute respiratory tract infection diagnoses for which antibiotics are not usually indicated [28].

### Outcome Measure

The primary outcome measure of interest is physicians’ monthly antibiotic prescribing rate. The antibiotic prescribing rate will be computed by dividing the number of patients prescribed antibiotics by the total number of patients with URTI seen by the physician in the month.

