### Sample Size

At the end of 12 months, all hospitals will be exposed to both interventions. Assuming 80 physicians per ED and an average of 1200 patients with URTI per ED over a 6-month period, a total of 640 physicians and 9600 patients will be exposed to the interventions in the 12-month intervention period.

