### Statistical Analysis

We will analyze the data using segmented regression models. Segmented regression models allow adjustments to confounding factor and slope changes at various time points but do not account for cluster differences. The inclusion of cluster differences will increase the robustness of the model [29]. The equation of the model is shown as follows:

β1 measures the preintervention slope, β_2,4,6,8_ measures the immediate change in mean outcome from the previous level, while β_3,5,7,9_ measures the difference in slopes pre-post compared with the previous level. β_11_ measures the differences in groups or clusters at the preintervention level, β_12,14_ measures the differences in groups or clusters on changes at the start of the intervention, while β_13,15_ measures the differences in groups or clusters on changes in slope due to the intervention. Statistical software such as SPSS (IBM Corp), STATA (StataCorp), and R will be used for analysis.

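### The primary outcome is a physician-month proportion resting on about 2.5 patients; the segmented model should be fitted to the counts, or its weighting and target stated

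*Protocol article*

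**What the plan says.** The Outcome Measure section states: "The primary outcome measure of interest is physicians’ monthly antibiotic prescribing rate". It forms the rate by "dividing the number of patients prescribed antibiotics by the total number of patients with URTI seen by the physician in the month". The denominator is thus one physician's URTI patients in one month.

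The Sample Size section gives the volumes: "Assuming 80 physicians per ED and an average of 1200 patients with URTI per ED over a 6-month period". From these it concludes that "a total of 640 physicians and 9600 patients will be exposed to the interventions in the 12-month intervention period".

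The Statistical Analysis section plans segmented regression with terms for differences between groups or clusters. One set of coefficients "measures the immediate change in mean outcome from the previous level". The equation itself is absent from the text available. The surrounding prose names no distribution, link, weight or minimum denominator, and no rule for a month in which a physician saw no URTI patient.

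**The concern.** A proportion based on two or three patients can take very few values, does not exist when the denominator is zero, and has a sampling variance that depends strongly on that denominator. A regression that treats each such rate as one equally reliable observation ignores all of this.

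Precision is at stake, because the noisiest rates would count as much as the most informative ones. So is the validity of standard errors that assume constant variance, particularly if URTI volumes differ between EDs or move over the 36 months. So is clarity about the target: an equally weighted analysis estimates an average over physician-months, and a count-based one gives more weight to months with more patients. If low-volume physicians respond differently, the two answers differ, and the protocol does not say which it wants.

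**Working it through.** **Reproducing the plan's totals.** 80 physicians × 4 EDs × 2 six-month periods = 640, and 1200 × 4 × 2 = 9600. Both match the Sample Size section.

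**Mean denominator.** 1200 / 6 = 200 URTI patients per ED-month, and 200 / 80 = 2.5 per physician-month. This assumes that all 80 physicians are active each month.

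**Distribution of denominators (assumption: Poisson with mean 2.5).**
- No URTI patient: exp(−2.5) = 0.082, or about 39 of the 80 × 6 = 480 physician-months per ED per half-year. With negative binomial volumes the share is 20% (k = 2) or 29% (k = 1).
- Among months with at least one patient, 22% rest on one patient and 50% on one or two. The one-patient months hold 8% of the patients (0.224 / 2.724).
- At the 35% prescribing rate that the Rationale cites from an earlier study at one hospital, about 49% of defined rates are exactly 0% or 100%.

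**Variance.** Take the variance of a rate on n patients as proportional to v(n) = ρ + (1 − ρ)/n, where ρ is the within-physician-month correlation. A one-patient rate then has 5.0 times the variance of a five-patient rate at ρ = 0, 1/0.28 = 3.6 times at ρ = 0.10, and 1/0.44 = 2.3 times at ρ = 0.30.

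**Information lost by equal weighting.** Over defined months, loss = 1 − 1/(E[v] × E[1/v]).
- Poisson, ρ = 0: E[1/n] = 0.499 and E[n] = 2.724, so the product is 1.359 and the loss is 1 − 1/1.359 = 26%.
- Poisson, ρ = 0.10: E[v] = 0.10 + 0.90 × 0.499 = 0.549 and E[1/v] = 2.213, so the product is 1.215 and the loss is 18%.

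| Volumes (mean 2.5) | ρ = 0 | 0.05 | 0.10 | 0.20 | 0.30 |
|---|---|---|---|---|---|
| Poisson | 26% | 22% | 18% | 12% | 8% |
| Negative binomial, k = 2 | 37% | 29% | 24% | 16% | 10% |
| Negative binomial, k = 1 | 43% | 34% | 27% | 18% | 12% |

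**Sensitivity to rotation.** If half the physicians were active in a month, the mean would be 5. With Poisson volumes, undefined months then fall to 0.7%, and the loss is 23% at ρ = 0, 12% at 0.10 and 4% at 0.30. With k = 1 it runs from 53% at ρ = 0 to 12% at 0.30.

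**The case against.** The strongest reply is that the fault is inferred. Nothing in the protocol says the rates are analysed unweighted, linearly or with constant variance. The equation is missing from the text, an analysis plan may exist, and coefficients on a mean outcome are compatible with weighted or binomial models. This stands, and it makes the loss and the standard-error point conditional. It does not remove the outcome definition, which the protocol does fix and which is fragile at the protocol's own volumes.

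The analysis unit could also be the ED-month, since the described coefficients refer to groups or clusters and to no physician term. The denominator would then be about 200 and the problem would largely vanish. The Outcome Measure section points to the physician-month, but the Statistical Analysis section does not confirm it.

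A reader might infer several stronger things that the documents do not support:
- *At least a quarter of the information is lost.* With Poisson volumes, 26% is the figure at zero correlation, and it falls as correlation rises.
- *Months without URTI patients are discarded data.* They contain no patients, and a count model learns nothing from them either. The defect is only that the outcome is undefined there.
- *One patient counts as much as ten.* A Poisson month with mean 2.5 reaches ten patients with probability 0.0003, so this needs uneven volumes. The sample feedback message does show such a physician ("You were the primary physician of 10 patients and 5 (50%) of them were prescribed with antibiotics") in a department-month of 200, but it is only an illustration.
- *A physician-average effect is a mistake.* The study population is physicians and the feedback concerns each physician's own rate, so that target is legitimate. It needs only to be declared.

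**Conclusion.** The point holds in conditional form. The mean denominator of 2.5 follows directly from the protocol, subject to all 80 physicians being active each month. The 8% of undefined months and the half of defined rates resting on one or two patients follow under Poisson volumes. If the segmented regression is fitted to these rates with equal weights, roughly 8% to 43% of the information is lost at that mean. Constant-variance standard errors then rest on an assumption that the denominators contradict; the size and direction of that error cannot be computed from the protocol. The correlation and the spread of volumes are assumed ranges, not trial data. It is not established that the plan uses equal weights. A count-based model is nonetheless a clear improvement on the natural reading of the text, and it needs no data beyond the visit and medication records already to be extracted.

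**What to change.** In Outcome Measure and Statistical Analysis:
- Keep the monthly rate for description and for the feedback messages.
- Fit the primary segmented model to the counts, either antibiotic yes/no per visit or numerator out of denominator per physician-month. Use a binomial model with a physician random intercept and ED effects.
- State that physician-months with no URTI patient do not contribute.
- Report model-based differences in percentage points.
- If a physician-average effect is the intended target, say so, and use variance-appropriate weights or robust standard errors clustered by physician.

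The cost is small but not zero. The coefficients in Statistical Analysis change scale and must be back-transformed, and a random-intercept logit effect is conditional on the physician, which is why the percentage-point summary matters. The study period ended in December 2023, before publication in February 2024, so the change should be documented as made before the outcome data are analysed.

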### Sample Size

At the end of 12 months, all hospitals will be exposed to both interventions. Assuming 80 physicians per ED and an average of 1200 patients with URTI per ED over a 6-month period, a total of 640 physicians and 9600 patients will be exposed to the interventions in the 12-month intervention period.

### Statistical Analysis

We will analyze the data using segmented regression models. Segmented regression models allow adjustments to confounding factor and slope changes at various time points but do not account for cluster differences. The inclusion of cluster differences will increase the robustness of the model [29]. The equation of the model is shown as follows:

β1 measures the preintervention slope, β_2,4,6,8_ measures the immediate change in mean outcome from the previous level, while β_3,5,7,9_ measures the difference in slopes pre-post compared with the previous level. β_11_ measures the differences in groups or clusters at the preintervention level, β_12,14_ measures the differences in groups or clusters on changes at the start of the intervention, while β_13,15_ measures the differences in groups or clusters on changes in slope due to the intervention. Statistical software such as SPSS (IBM Corp), STATA (StataCorp), and R will be used for analysis.

